### Data management plan

Patient health information (PHI) will be obtained directly from the patient and the electronic medical record (EMR). This information will only be obtained after documented informed consent has been provided by the patient. PHI will be stored in the Prisma Health RedCap^®^, a HIPAA compliant cloud platform. All data will be housed within the Prisma Health system. Surveys and questionnaires will be stored in a locked file cabinet in a locked room in the Human Performance Laboratory.

### Trial oversight

This study has been approved by the Institutional Review Board at the Prisma Office of Research Compliance and Administration (ORCA). All adverse events (AE) and serious adverse events (SAE) will be recorded from the start of the visits, beginning with the first visit for lactate threshold testing and throughout completion of exercise visits, or when the participant has elected to no longer participate. The investigators will record and report all AE and SAE to the IRB within 24 hours. Fatal or life threatening unexpected adverse reactions will be reported to Prisma Health IRB immediately.

## Discussion

With limited studies of mitochondrial function (e.g., oxygen delivery and utilization) during cancer chemotherapy, opportunity exists to address mechanisms of cachexia and cancer-related fatigue using NIRS. To date, two main studies used NIRS with cancer populations. However, neither of the research teams collected data during active chemotherapy treatment, and they only measured steady-state values during exercise as opposed to collecting oxygen kinetics during recovery and exercise. Additionally, the independent variables included treatments additional to chemotherapy, including radiation and immunotherapy. The variation in independent variables may have been the reason for limited changes in the NIRS outcome variables. Ederer et al [29] found significant differences in HHb and total hemoglobin with a limited sample size of 8 cancer survivors compared to matched controls, while Grigoriadis et al. [30] found no significant differences in any of the NIRS variables. Understanding oxygen delivery and utilization kinetics with ventilatory and local NIRS measurements during chemotherapy could unlock mechanistic understanding of mitochondrial dysfunction. Our study will be the first to recruit at least 30 patients diagnosed with cancer and capture both baseline and longitudinal NIRS measurements throughout the entire chemotherapy protocol.

The study’s design must consider 1) exercise tolerance levels to obtain fatigue and recovery kinetics for patients going through chemotherapy and 2) rapid recruitment of patients for baseline measurements. We recognize that the level of conditioning our patients have at baseline may be reduced as treatment progresses. Therefore, we chose a protocol that was tolerable to patients, which is to cycle to 10% above their lactate threshold level; both before discontinuing the LT test and for the on/off kinetics tests. This intensity elicits an appropriate mitochondrial response in the exercising muscle while allowing for a reasonable exercise intensity that a patient can complete despite anticipated treatment deconditioning. Additionally, because patient recruitment will occur at the time of diagnosis, a team of referral coordinators, nurse navigators, and oncologists need to identify newly diagnosed patients, and be prepared, through a “chemo-teach”, to consent interested patients in a timely manner.

A few limitations are to be considered regarding the validity of the PortaMon by Artinis Medical Systems. First, the device is designed to accurately penetrate 20 mm of depth through adipose tissue and into the muscle belly. If the subcutaneous adipose tissue thickness is greater than 20 mm, the infrared signal from the device will not penetrate the skeletal muscle body and be unable to obtain accurate measurements. Our protocol minimizes this concern by excluding participants who have greater than 20 mm adipose tissue subcutaneous to the vastus lateralis, and by standardizing device placement on the leg from test to test to increase reliability and validity of repeated measures measurements. Ambient light can interfere with the signal quality, however Oxysoft provides real-time data acquisition (DAQ) measurements. Using the manufacturer’s recommendation, channels with DAQ higher than 97% will be removed from analysis.

Results from this pilot study will provide information on the feasibility of capturing on/off kinetics mitochondrial function data longitudinally using NIRS in patients newly diagnosed with breast or gynecological cancer, provide preliminary data for future extramural funding, and inform the scientific community of results through dissemination via conference presentations and peer-reviewed journal publications.

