Assessment of mitochondrial capacity with NIRS includes studies of clinical populations with peripheral artery [27], chronic kidney [24], and neurologic diseases such as traumatic spinal cord injury and multiple [22], as well as comparisons with healthy [28] and age-related differences in skeletal muscle oxidative [17]. However, there is a dearth of NIRS studies examining the effects of chemotherapy on skeletal muscle mitochondrial function in patients with cancer. Only two studies to our knowledge have utilized NIRS to measure muscle oxygenation variables in cancer survivors. Ederer, et al. [29] determined that [HHb] and [Hb]total were significantly lower in eight cancer survivors (all eight received chemotherapy and five received radiation) compared to healthy controls during exercise at ventilatory threshold. Grigoriadis et al. [30], did not find a significant difference in muscle oxygenation variables between 23 patients with breast cancer (16 received chemotherapy, nineteen received radiation therapy, and 21 received hormonal therapy) and 23 participants who served as age and BMI matched controls. Recent literature of near infrared spectroscopy related to cancer primarily involves detection and identification of cancerous [31] or the use of near infrared light as a photoimmunotherapy [32]. Therefore, the hypothesized loss of mitochondrial capacity throughout chemotherapy treatment has not been studied longitudinally starting at baseline and tracking through the chemotherapy regimen in breast and gynecologic cancer patients with NIRS to date.

The aims of our study are to develop a protocol that 1) assesses mitochondrial dysfunction in cancer patients using exercise that is tolerable for the patients throughout the entire chemotherapy regimen and 2) observe the changes in mitochondrial functional capacity between different chemotherapy regimens for each chemotherapy cycle. The protocol also will help us evaluate a potential correlation between subjective self-reported fatigue and perceived effort with corresponding objective whole-body metabolic measurements and NIRS measurements. The proposed study will help inform clinical decision makers in the oncology community regarding current chemotherapy regimens (based upon the National Comprehensive Cancer Network, NCCN) that patients may best tolerate for cachexia and fatigue.

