### Participants and eligibility requirements

Participants recruited for this study will be female patients with breast cancer or gynecological cancer who will undergo a standard of care chemotherapy treatment as directed by their oncologist. Participants are all women who are undergoing adjuvant therapy, meaning that gynecological and breast cancer patients are not presenting clinical evidence of disease (non-metastatic) therefore can be considered from the same population for modeling purposes. Additionally, treatment regimens for these patient populations are similar based on NCCN guidelines which warrants modeling them together. Participants who are cleared by their oncologist to participate will be recruited through informative pamphlets and by oncology nurses trained in research and human subjects protection in Prisma Health System’s Cancer Institute at Greenville Memorial Hospital, as well as Prisma Health affiliated oncologists’ offices. Participants will be informed of the study’s purpose, availability, timeline, and potentially associated minimal risks. Study staff will then obtain written informed consent from participants who agree to participate and before any data collection. Patient inclusion and exclusion criteria are listed in Table 1.

**Table 1 pone.0315351.t001:** Inclusion and exclusion criteria.

Inclusion Criteria
Female patients diagnosed with breast cancer or gynecological cancer without distant metastasis
Age > 20 years old
Able to perform exercise on a stationary cycle ergometer at moderate intensities for a maximum of 15 minutes
Hemoglobin (Hb) values > 10 g/dl at baseline
Alanine aminotransferase (ALT) and Aspartate transferase (AST) values less than 2.5X the upper limit of normal by institutional standards
Godin-Shephard Leisure Time Physical Activity Questionnaire (GLTEQ) score of 14 or higher
Exclusion Criteria
Metastatic breast or gynecological cancer
Clinically advanced cardiovascular disease or pulmonary disease or disease requiring continuous oxygen supplementation
Greater than 2 centimeters of subcutaneous adipose tissue on the anterior thigh
Inability to walk or stand, movement disorders, spinal cord injuries
Autoimmune disorders
Pregnant or breastfeeding
Mini-Mental State Examination (MMSE) score < 24
History of chemotherapy within 5 years prior to beginning participation

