### Observational protocol for first and subsequent visits

Before starting chemotherapy, patients will undergo baseline testing that includes a lactate threshold test and an ON-OFF kinetics exercise test. The lactate threshold test will determine the power output (110% power at lactate threshold, P_LT+_) to be used for the follow-up baseline on-off kinetics test (ON-OFF). The ON-OFF kinetics test will take place at least 24 hours after the lactate threshold test and consist of 3 cycles of 2 minutes at P_LT+_ and 2 minutes of complete rest. Whole body O_2_ uptake and CO_2_ production will be captured via a metabolic cart during each test. Testing will take no more than 60 minutes per session, with a maximum study total of 300 minutes (about 5 hours) of participation per patient. Patients will be requested to avoid exercise and use of certain substances (tobacco, alcohol, caffeine, and contraindicated medications) 24 hours before testing. If laboratory baseline evaluation cannot be completed prior to the participant’s treatment initiation, treatment will not be delayed, and patients will be waived from the study.

The independent variables in this study are drug regimen and number of chemotherapy treatments. The dependent variables in this study will be the changes in O_2_Hb, HHb, and TSI of the vastus lateralis, indicative of mitochondrial oxidative capacity after a bout of cycling. The specific variables measured will be the average recovery kinetics time constant, τ, and TSI. Indirect calorimetry (O2 uptake, CO2 production) also will be captured at rest and during the ON/OFF kinetics as control variable comparisons for whole-body O2 uptake and utilization.

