We will analyze the *ΔO*_*2*_*Hb,* Δ*HHb,* and *ΔTSI*, calculated as the change in steady state levels of O_2_Hb, HHb, and TSI respectively from work to rest, with steady state values calculated as the mean value of the final thirty seconds of the stage. For each data set of one on-off kinetics, there will be three work/rest period pairs therefore we will calculate three delta values and average the three delta values to obtain one delta value for O_2_Hb, HHb, and TSI per data set. The three work/rest transitions will allow for reliability testing with intraclass correlation coefficients. For participant data to be included in the final analysis, the participant will need to complete at least three on-off kinetic laboratory visits. Each participant will complete an on-off kinetics at least two weeks apart, but not more than one month apart in accordance with their prescribed chemotherapy treatment regimen. Each on-off kinetics will correspond with the first infusion of a chemotherapy cycle. To allow participants a maximum amount of time to recover from infusions before participating in exercise, the corresponding on-off kinetics takes place within 48 hours of the first infusion of the subsequent chemotherapy cycle. Since chemotherapy treatments vary depending on oncologist recommendation, each participant may complete different lengths of treatment, resulting in each participant having different numbers of data points. This will prevent us from using traditional statistical analysis such as repeated measures ANOVA. Since it is not time itself, but rather the compilation of chemotherapy infusions over time that we predict will cause changes in measures of mitochondrial oxidative function, we will treat the number of chemotherapy cycles as an ordinal variable in this analysis. We will complete an analysis using mixed effects models to predict τ and deltas from the number of chemotherapy treatments with a random intercept for patients. For aim 2, ANOVAs will be used to assess differences in mitochondrial capacity between drug regimens at each chemotherapy cycle.

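### Radiation or hormonal therapy that starts or stops during the tested cycles is neither restricted nor accounted for, so the Aim 1 cycle trend cannot be credited to chemotherapy infusions alone

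*Protocol article*

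**What the plan says.** The Discussion reviews two earlier NIRS studies in cancer. It notes that "the independent variables included treatments additional to chemotherapy, including radiation and immunotherapy" and continues: "The variation in independent variables may have been the reason for limited changes in the NIRS outcome variables". The Introduction gives the treatment mix in one of them, a cohort of 23 patients with breast cancer: "16 received chemotherapy, nineteen received radiation therapy, and 21 received hormonal therapy".

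For this trial:

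- **Eligibility.** In Participants and eligibility requirements, the only treatment history restricted in Table 1 is "History of chemotherapy within 5 years prior to beginning participation". The same section states "Participants are all women who are undergoing adjuvant therapy". Radiation, hormonal therapy and surgery do not appear in the criteria.
- **Variables.** Under Observational protocol for first and subsequent visits: "The independent variables in this study are drug regimen and number of chemotherapy treatments".
- **Aim 1 model.** Data analysis and statistical analysis will "predict τ and deltas from the number of chemotherapy treatments with a random intercept for patients".
- **Interpretation.** The same section says "it is not time itself, but rather the compilation of chemotherapy infusions over time that we predict will cause changes".
- **Length of follow-up.** Sample size describes 3–4 cytotoxic cycles and a further 3–4 non-cytotoxic cycles, and says concurrent treatment could form its own group.

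**The concern.** Aim 1 has no untreated comparison group. Its evidence is the within-patient trend of τ and the deltas over cycle number. Anything else that changes in step with cycle number enters that coefficient. The plan recognises added treatments as a possible source of unclear results elsewhere, but neither limits radiation or hormonal therapy nor has a term for either when it begins or ends between tests.

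If such changes are common, the cycle coefficient mixes chemotherapy with them. The direction is not fixed: depending on how the co-treatment acts on τ, it could mimic a loss of oxidative capacity or hide one. This matters because the power statement refers to an effect of chemotherapy on τ, and the Introduction says the results will inform decision makers about regimens.

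**Working it through.** **1. The plan's own figure.** The sample size of 30 for power 0.8 cannot be reproduced, because the mean slope, slope SD, number of visits and alpha are not stated. The point does not depend on it. The inputs taken from Sample size are n = 30, error SD 5.54 s, and a gamma intercept with shape 1.57 and scale 12.5.

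**2. Which exposures bias the slope.** For patient i at cycle c, write

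τ_ic = a_i + β·c + γ·E_ic + error,

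where E is co-treatment status. If E does not change over the tests, γ·E is a constant and goes into a_i, so β is unaffected. If E switches on or off during follow-up, it is correlated with c and part of γ is loaded onto β. Completed past radiation with a stable effect is therefore largely harmless; co-treatment that changes between tests is not.

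**3. Size, on assumed inputs.** The documents give neither the share of affected tests nor the shift in τ. Shift in the late-cycle mean = share × shift:

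- 0.20 × 5 s = 1.0 s
- 0.40 × 8 s = 3.2 s

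Yardstick: SE of a mean change from baseline in 30 patients, residual error only = 5.54 × √2 / √30 = 1.43 s. Between-patient variation in slope would increase it.

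**4. Effect on the test, on assumed inputs.** 20,000 trials of 30 patients were simulated with a chemotherapy effect of zero, an assumed slope SD of 1 s/cycle, error SD 5.54 s, and a drift of 2 s/cycle from another cause in a share of patients. The mean within-patient slope was tested at two-sided 0.05.

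| Share with drift | False cycle effect | Significant, 4 visits | Significant, 6 visits |
|---|---|---|---|
| 0 | 0 | 5% | 5% |
| 0.25 | 0.25 × 2 = 0.5 s/cycle | 16% | 29% |
| 0.50 | 0.50 × 2 = 1.0 s/cycle | 46% | 78% |

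This shows the mechanism. It does not predict what this trial will find.

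**5. Would adjusting for weeks since surgery help?** Within a patient, weeks since surgery = (surgery-to-baseline interval) + (cycle length × cycle), which is almost a linear function of cycle. Inputs: n = 30, 4 visits, error SD 5.54, intercept SD = 12.5 × √1.57 = 15.66, and an assumed 3 to 8 week interval from surgery to baseline. Without the covariate, the SE of the cycle slope is 5.54 / √(5 × 30) = 0.45 s/cycle, where 5 is the sum of squares of cycles 0 to 3 about their mean. With it:

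- cycle lengths spread evenly over 2, 3 and 4 weeks: about 3.6 times larger (0.45 × 3.6 ≈ 1.6 s/cycle)
- mostly 3-week cycles: about 6 times larger
- all 3-week cycles: about 14 times larger

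That covariate would remove most of the information about the cycle effect.

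**The case against.** The strongest reply is that the design already differs from the studies it criticises. As the article describes them, those compared patients or survivors with controls, so treatment history entered the contrast directly. Here each woman is compared with her own pre-chemotherapy baseline. The Discussion first faults the earlier work for not measuring during active chemotherapy and for using only steady-state values; mixed treatment comes after that and is hedged. Immunotherapy, also named in the quoted sentence, is partly handled as a possible regimen group. All of this stands, and it confines the point to co-treatment that changes during follow-up.

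Nor does any document show that radiation or hormonal therapy begins within the test window. Tests are tied to chemotherapy infusions, and the counts of 19 and 21 out of 23 describe another cohort's treatment history. This also stands: the share of affected tests could be small. But the plan as stated would not reveal it either way.

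A reader might go further and infer that every baseline is taken in women still recovering from surgery, and that recovery would shorten τ and hide a real loss. The documents do not support this. Surgery is not mentioned and is only inferred from the adjuvant setting. The Discussion says recruitment occurs at diagnosis, which leaves the timing unclear. Entry requires oncologist clearance, the ability to cycle at moderate intensity and a minimum activity score. No effect of recovery on τ is given.

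Finally, this is a condensed article on a pilot, and covariates are often left to a fuller document. That carries limited weight here, because eligibility, independent variables, the Aim 1 model and the causal reading are all stated in the article.

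**Conclusion.** The concern holds in a limited form. The plan neither restricts radiation or hormonal therapy nor accounts for either when it starts or stops during the tested cycles, yet it attributes the within-patient cycle trend to accumulated infusions. Stable past exposures are not the problem.

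The size is unknown. The 1.0 to 3.2 s range and the false-positive rates rest wholly on assumed shares and shifts. They show only that plausible-looking inputs would be comparable with the 1.43 s standard error. A claim that the study simply repeats the weakness it criticises would go too far, given the within-patient baseline.

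The point should be addressed before the final analysis because the correction is cheap and can still be made: Trial status reports 26 completers of a planned 30, so it is late for an eligibility change but not for using recorded dates.

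**What to change.** 1. Extract start and stop dates of radiation and hormonal therapy, and the date of any cancer surgery, from the electronic medical record that the Data management plan already uses.
2. In Data analysis and statistical analysis, prespecify two fits of the Aim 1 model: one on tests before any radiation or hormonal therapy starts, and one on all tests. State how women whose co-treatment was completed or already under way at baseline are classified, and count separately those in whom it ends during follow-up.
3. Report how many tests and patients are affected, including any who fall below the three-visit minimum in the restricted fit.
4. If the two fits differ, or many tests are affected, describe the Aim 1 result as change during treatment rather than an effect of chemotherapy alone.
5. Do not add weeks since surgery to the main model, for the reason in step 5 of the working. Report the surgery-to-baseline interval descriptively.

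Cost: date extraction from records already accessed and one additional model fit, with no new visits. The downside is that some late tests, and possibly a few patients, leave the restricted analysis, so its estimate will be less precise.

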### Trial status

The trial is currently in the data collection phase with 26 participants who have completed the protocol. The study is planned to continue to enroll test subjects until n = 30.
